### Eligibility and recruitment

2.3

Participants will be recruited from nursing home in Changchun, Jilin Province, China. The old patients with disabilities in nursing homes will be recruited through live lecture, poster promotion and official account by researchers and staff. Eligible subjects will be screened through face-to-face surveys. Inclusion criteria for participants will be: (1) Will be aged ≥60 years; (2) Will reside in a nursing home; (3) Will be classified as having mild to moderate disability according to the Ministry of Civil Affairs’ National Standard for Elderly Ability Assessment; (4) Will volunteer to participate in the study and sign informed consent. Participants will be excluded if: (1) Older adults with severe cognitive impairment or severe mental disorders who are unable to comply with the study procedures; (2) Older adults with severe hearing or visual impairments that prevent clear and fluent communication.

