### Randomization, allocation and blinding

2.4

Participants will be randomly allocated to the intervention or control groups in a 1:1 ratio using computer-based permuted block randomization. The randomization sequence will be generated by an independent research coordinator, and the details of group allocation will be concealed on cards placed inside sequentially numbered, sealed opaque envelopes. Outcome evaluators, and data analysts will be kept blinded.

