#### Quantitative outcome measures

2.6.1

The participants in both the intervention and control groups will be assessed on their intrinsic capacity, covering six domains, including cognitive function, motor function, vitality, vision, hearing, and depression. Assessments will be conducted at T_0_, T_1_, and T_2_. For a detailed description of data collection, refer to Table 2.

**Table 2 tab2:** Overview of data collection.

Measures	T_0_	T_1_	T_2_
Demographics	△		
ICOPE screening tool	△	△	△
MMSE	△	△	△
SPPB	△	△	△
MNA	△	△	△
Visual acuity test	△	△	△
Hearing test	△	△	△
PHQ-9	△	△	△

T_0_, pre-intervention (week 0); T_1_, post-intervention (week 12); T_2_,1-month follow-up (week 16); ICOPE, Integrated Care for Older People; MMSE, Mini-Mental State Examination; SPPB, Short Physical Performance Battery; MNA, Mini Nutritional Assessment; PHQ-9, Patient Health Questionnaire-9.

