### Statistical analysis

2.8

For quantitative analysis, Epidata 3.1 (Epidata Association) will be used for double data entry and SPSS 26.0 (International Business Machines Corporation, IBM) will be used for data analysis and processing. Descriptive statistics will be used to describe participants’ characteristics and mental health outcomes. For continuous variables, the Shapiro–Wilk test (S-W test) will be used to assess normality. Depending on the results of the S-W test, the mean and standard deviation or the median and the interquartile range will be used for descriptive statistics. For categorical variables, frequencies and percentages will be reported. Independent samples *t*-tests, Mann–Whitney U tests and χ^2^ tests will be used to compare outcome results and baseline data. Paired sample t-tests or non-parametric rank sum tests will be used to compare the outcomes within the group. To analyze between-group differences, a two-independent sample t-test or a Mann–Whitney U rank sum test will be used. The changing trend of the outcome indicators of the study subjects will be measured between T_0_, T_1_, and T_2_; the inter-group factor will be the subgroup (intervention group and control group), the intra-group factor will be the measurement time point (T_0_, T_1_, and T_2_), and the interaction will be the group × time point. A generalized linear mixed model will be used for analysis. In addition, age, frailty status, and other relevant variables will be included as covariates, depending on data availability and implementation feasibility, to control for their potential confounding effects. The significance level of all the above statistical tests will be set at *p* ≤ 0.05, indicating a significant statistical difference.

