However, this study will also face some challenges. First, many nursing homes face imbalanced resource and funding allocation, with some lacking the necessary equipment, technical support, and staff for the intervention (48). To address this issue, the research team plans to apply for special funding to support the project. Furthermore, the team will work to optimize the internal resource allocation of institutions and develop tailored solutions based on the specific circumstances of each facility. Second, the long-term care intervention program covers multiple health aspects, requiring caregivers to have advanced knowledge and skills. However, inconsistent training in some nursing homes limits the program’s effectiveness. To address this, we plan to develop a comprehensive training program, offer expert-led courses, and regularly assess caregivers’ performance. Thirdly, each old patients with disabilities have different health conditions and needs, and existing standardized intervention programs may struggle to address individual differences (42). To overcome this challenge, this study will develop flexible and personalized interventions, adjusting them according to each older adult’s health status and needs. Fourth, the scales used are self-reported measures, which can be subject to bias. Factors such as acute illness, changes in physical function, and stressful events can impact the accuracy of participants’ responses (49). Therefore, if conditions permit, objective indicators, such as physiological indicators, will be considered alongside self-reported measures, to reduce the bias of individual subjective feelings and improve the objectivity of the assessment. Fifth, this study may be subject to selection bias, as participants are drawn from specific nursing homes that may not fully represent the broader population of older patients with disabilities. To minimize this risk, we will seek to recruit participants from multiple institutions with diverse characteristics. Finally, the old patients with disabilities in the control group will maintain their routine life and standard care practices within the nursing home. While this mirrors real-world practice, the lack of an active or attention-matched control may overestimate the intervention’s effect due to non-specific factors like increased attention or support, and this may affect internal validity.

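### The planned group × time model treats the T0 score as an outcome, which is less precise than adjusting for it, and the covariate rule is open-ended and names frailty without describing a measure of it

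*Protocol article*

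**What the plan says.** **Model.** Section 2.8 names the group as the between-subject factor, and "the intra-group factor will be the measurement time point (T_0_, T_1_, and T_2_), and the interaction will be the group × time point". It continues: "A generalized linear mixed model will be used for analysis". T0 is therefore a repeated outcome. No link function is stated, and nothing holds the two arms to a common mean at T0. The Abstract gives the primary outcome as change in intrinsic capacity, judged by a mean difference.

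**Covariates.** The same section says that "age, frailty status, and other relevant variables will be included as covariates, depending on data availability and implementation feasibility", with the purpose "to control for their potential confounding effects".

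**Data held.** Section 2.6.1 says: "For a detailed description of data collection, refer to Table 2". Table 2 lists demographics, the ICOPE screening tool, MMSE, SPPB, MNA, visual acuity, hearing and PHQ-9. Sections 2.6.1.1 to 2.6.1.8 describe no frailty instrument, and neither does section 2.3. Section 2.3 does record disability grade at screening: "Will be classified as having mild to moderate disability".

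**Homes and randomisation.** Section 2.3 refers to a nursing home in the singular. The Discussion says "we will seek to recruit participants from multiple institutions with diverse characteristics". Section 2.4 allocates "using computer-based permuted block randomization" and names no stratification factor.

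**The concern.** Two features of section 2.8 fix the analysis less well than they could.

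First, the earlier score of the same outcome is usually the best single predictor of the later score. A model with free group means at T0 uses that score only by subtraction. Subtraction over-corrects whenever r is below 1, and the cost is a wider confidence interval for the main contrast.

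Second, the covariate rule is stated but not closed. It names one variable that can be taken from demographics (age), one for which no measurement is described (frailty), and an unnamed remainder whose inclusion depends on circumstances during the trial. A reader of the results could not tell which adjusted model had been planned. The stated aim of controlling confounding also does not help choose the set: in a randomised comparison, the reason to adjust is precision and chance imbalance, which points to strong baseline predictors held for everyone.

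**Working it through.** **1. The plan's own figure.** Section 2.2 gives f = 0.25, α = 0.05, power 0.90, three measurements, two groups and correlation 0, and states N = 70. For the within-between interaction, λ = f² × N × m / (1 − ρ) = 0.0625 × 70 × 3 / 1 = 13.125, on 2 and (70 − 2) × 2 = 136 degrees of freedom (sphericity assumed). Power is 0.904; at N = 68 it is 0.895. So 70 is reproduced, and the present point does not alter it.

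**2. What the T1 contrast estimates.** With complete data and an identity link, free group means at T0 and T1 make the group × time term the difference between arms in mean (T1 − T0).

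**3. Variance of the two contrasts.** Take equal variance σ² at each time, correlation r, and n per arm. The common factor 2/n cancels.

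- Change score: σ² + σ² − 2rσ² = 2σ²(1 − r)
- Baseline as covariate: σ²(1 − r²)
- Ratio: (1 − r)(1 + r) / [2(1 − r)] = (1 + r)/2

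A mixed model with a common T0 mean in both arms has essentially the same efficiency as the covariate form.

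**4. Numbers.** The document gives no T0–T1 correlation for the analysis, so r is an assumed range. The 0.5 SD effect in the power columns is also an assumption. Power is from the noncentral t with the planned 35 per arm, two-sided 0.05.

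| r (assumed) | Change, 2(1−r) | Adjusted, 1−r² | Ratio | Power, change | Power, adjusted |
|---|---|---|---|---|---|
| 0.3 | 1.40 | 0.91 | 0.65 | 0.41 | 0.58 |
| 0.5 | 1.00 | 0.75 | 0.75 | 0.54 | 0.66 |
| 0.7 | 0.60 | 0.51 | 0.85 | 0.76 | 0.82 |
| 0.9 | 0.20 | 0.19 | 0.95 | above 0.99 | above 0.99 |

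At r = 0.5 the change-score contrast needs 1/0.75 = 1.33 times as many participants for the same precision. At r = 0.9 the factor is 1/0.95 = 1.05. The r = 0 in section 2.2 is described there as a conservative planning setting, so it is not used here as an expected value; the ratio at that point would be 0.50.

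**5. The covariate rule against the data described.**

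| Variable | Named in 2.8 | Measurement described |
|---|---|---|
| Age | yes | demographics at T0, and eligibility |
| Frailty status | yes | none found |
| Other relevant variables | not identified | cannot be checked |
| T0 value of each outcome | as an outcome level only | Table 2, T0 column |
| Disability grade | no | screening, section 2.3 |

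**6. Adding age or grade does not recover the lost precision.** A time-constant covariate entered as a main effect adds the same amount at T0 and T1, so it cancels from T1 − T0. In the complete-data linear case the group × time estimate is then unchanged. Such covariates act on the contrast only if they interact with time, if data are missing, if the link is not the identity, or if the analysis is of follow-up values.

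**The case against.** The strongest defence is that both estimators are valid and unbiased under randomisation, so the choice is one of efficiency. That stands. Three qualifications also stand: r is not given, the gain almost vanishes when r is high, and the formula needs an identity link and complete data. The ICOPE total is a 0–5 sum of binary domains and 2.8 names no link, so the ratio is exact only for outcomes analysed on their own scale.

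Several stronger readings are tempting, and the document does not support them.

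- **A reader might infer that the baseline score is unused.** It is used, as the first level of the time factor. The point is only how it is used.
- **A reader might infer that frailty cannot be fitted.** Table 2 is an overview and is not exhaustive: adherence, adverse events and satisfaction are planned in 2.6.1.8 but are not in it. What can be said is that the article describes no frailty measure.
- **A reader might infer that covariates will be picked after outcomes are seen.** The text does not say so, and section 2.4 keeps data analysts blinded. Blinding limits selection in favour of one arm, but it does not replace a fixed list.
- **A reader might infer that the blocks are unstratified and that a home effect is ignored.** Section 2.4 is silent on stratification, the Discussion states only an aspiration to use several homes, and an article commonly leaves such detail to the full protocol. Disability grade and home could also fall among the unnamed variables.

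The defence does not remove the open rule itself. Section 2.8 writes a covariate rule and makes it conditional, which differs from leaving the list to another document.

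**Conclusion.** The point holds as one of precision and pre-specification, not of validity. The T1 contrast in section 2.8 has more variance than a baseline-adjusted contrast from the same data. Adjustment would cut the variance by 35%, 25%, 15% or 5% at r of 0.3, 0.5, 0.7 or 0.9. These figures assume equal variances, complete data and an identity link. The power figures further assume a 0.5 SD effect and 35 per arm. The size for this trial is undetermined because r is not given.

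Separately, the covariate list is open, and it names a variable with no described measurement. That rests on the text alone. No loss is claimed from omitting disability grade or nursing home, because the article gives nothing from which to size it. The stated sample size is unaffected.

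**What to change.** In section 2.8:

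1. Analyse T1 and T2 with the T0 value of the same outcome as a covariate, or keep T0 as an outcome and constrain a common T0 mean across arms in the mixed model.
2. Fix the other covariates in advance from data held for every participant: age, and disability grade from screening. State how they enter; if T0 stays as an outcome, they need an interaction with time to act on the contrast.
3. Delete frailty status, the unnamed remainder and the clause on availability and feasibility.
4. If more than one nursing home takes part, add nursing home to the model. Stratifying the blocks by home is optional and is not needed for this point.

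The cost is a few sentences in 2.8, settled before unblinding. No new data, visits or participants are required.

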**Methods:**

This mixed-methods study will employ an explanatory sequential design, starting with a quantitative evaluation using a randomized controlled trial (RCT), followed by a supplementary qualitative study. The old patients with disabilities will be randomly allocated in a 1:1 ratio into the intervention group or the control group. The old patients with disabilities in the intervention group will participate in a 12-week “ICOPE-Based Long-Term Care Intervention Program,” and in the control group will maintain their routine life and standard care practices. Participant outcomes in both conditions will be assessed at pre-intervention (T_0_, week 0), post-intervention (T_1_, week 12), and 1 month after the intervention (T_2_, week 16), and a generalized linear mixed model will be used for analysis. The primary outcome is the change in intrinsic capacity, with the significance of the mean difference assessed to determine the intervention effect. In the qualitative part of this study, interviews will be conducted with old patients with disabilities from the intervention group at T_1_ to explore their experiences of receiving the intervention, and content analysis will be applied to the data collected.

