Currently, practice-based projects centered around intrinsic capacity, at the heart of the ICOPE framework, are being gradually launched to improve the quality of care for older adults. These ICOPE practice projects have been implemented in multiple countries worldwide, including France (21) and South Korea (22), achieving significant results. In China, researchers such as Ma et al. (23) conducted a study on 976 middle-aged and older adults (aged 50–97) enrolled in the ICOPE-China project, using the ICOPE screening tool for intrinsic capacity assessments. The study found that 69.1% of participants showed a decline in intrinsic capacity, validating the tool’s effectiveness in identifying declines in the intrinsic capacity of older adults and providing valuable insights for the further development of older adult care in China. Overall, while domestic projects primarily focus on the initial screening of intrinsic capacity, there is still a lack of systematic research and practical application regarding the design and implementation of comprehensive care pathways and intervention programs, particularly for old patients with disabilities in nursing homes.

The main aim of this study is to explore the effects and the experiences of using “long-term care intervention program based on ICOPE for old patients with disabilities in nursing homes” in old patients with disabilities. An explanatory sequential design will be used, starting with a RCT investigating the impact of a long-term care intervention program on intrinsic ability (motor function, cognitive function, psychological function, sensory function, and nutrition) in a group of old patients with disabilities. Subsequently, qualitative surveys will be conducted to gain an in-depth understanding of participants’ subjective experiences of participating in this exergame intervention, in particular the benefits arising from the intervention as well as the influencing factors for participation, which will help understanding the mechanisms behind the therapeutic effects. This information will provide a basis for optimizing, refining, and promoting long-term care intervention program.

We hypothesis that participants in the long-term care intervention program group will experience an improvement of intrinsic ability, compared to those in the control group. Furthermore, we anticipate that these improvements will be maintained at 1-months follow-up.

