##### ICOPE intrinsic capacity screening tool

2.6.1.1

The assessment of intrinsic capacity strictly follows the five domains proposed by the WHO (33): cognition function, motor function, sensory function (Vision and Hearing), vitality, and psychological function. Each domain is scored as 0 (normal) or 1 (impaired), and the total intrinsic capacity score is the sum of the five domain scores, ranging from 0 to 5. A score of 3 to 5 is defined as low intrinsic capacity, while a score of 0 to 2 is classified as high intrinsic capacity. Specific contents include: ① Cognitive function: Screening assesses memory and temporal orientation, including word recall (flower, door, rice), time and place orientation, and short-term memory tests. An incorrect response or failure to recall all three words indicates a positive screening result. ② Motor ability: The chair rise test is used to assess mobility. Participants must stand up and sit down five times consecutively without using their arms for support, completing the task within 14 s. Failure to meet this requirement is considered a positive screening result. ③ Nutrition: Assesses weight changes and dietary habits over the past 3 months, including whether the individual has experienced weight loss of ≥3 kg or frequently finds food tasteless or difficult to swallow. A “yes” to either question indicates a positive screening result. ④ Vision: Assess whether there are visual difficulties (e.g., watching TV, reading, or recognizing faces) or a history of eye disease treatment. A positive response to either indicates a positive screening result. ⑤ Hearing: Use the whisper test or inquire about subjective hearing perception. Failure in the test or a significant perceived decline in hearing is considered a positive screening result. ⑥ Depression: Assess recent emotional state, including feelings of low mood, depression, or hopelessness, or loss of interest in daily activities. The presence of these symptoms indicates a positive screening result.

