## Conclusion

4

Compared to the control group, old patients with disabilities who receive the long-term care intervention program may show improvements in intrinsic capacity, specifically in areas such as motor function, cognitive function, nutrition, sensory function, and psychological function. If proven effective, the intervention program could offer a practical solution to the complex health needs of older adults with disabilities, improving their well-being and reducing caregiver and healthcare burdens. Findings from the qualitative study will further inform the refinement of the intervention, improving its effectiveness, adaptability, and user satisfaction. Clinically, this study supports the integration of person-centered, function-oriented care into long-term care practice, and encourages the adoption of the ICOPE framework as a structured model.

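### The primary outcome, change in intrinsic capacity, is not tied to the 0–5 ICOPE total or any other measure, while seven unranked measures of it are each tested at p ≤ 0.05

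*Protocol article*

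**What the plan says.** The abstract gives one primary outcome, in the singular: "The primary outcome is the change in intrinsic capacity, with the significance of the mean difference assessed to determine the intervention effect". It names no instrument.

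Section 2.6.1 states that participants will be "assessed on their intrinsic capacity, covering six domains, including cognitive function, motor function, vitality, vision, hearing, and depression". Table 2 lists seven measures, each taken at T0, T1 and T2: the ICOPE screening tool, MMSE, SPPB, MNA, visual acuity, hearing and PHQ-9. None is marked primary, secondary or exploratory.

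Section 2.6.1.1 is the only place where intrinsic capacity becomes a single number: "the total intrinsic capacity score is the sum of the five domain scores, ranging from 0 to 5". It counts five domains, where Section 2.6.1 counts six.

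Section 2.8 sets a single rule for the t-tests, rank tests, χ² tests, paired tests and mixed model alike: "The significance level of all the above statistical tests will be set at" p ≤ 0.05.

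The Introduction states the aim by domain, as an effect "on intrinsic ability (motor function, cognitive function, psychological function, sensory function, and nutrition"). The Conclusion expects that treated participants "may show improvements in intrinsic capacity, specifically in areas such as motor function, cognitive function, nutrition, sensory function, and psychological function".

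**The concern.** The seven measures can disagree. SPPB might improve while the ICOPE total and MMSE do not, and the article does not say whether the trial would then be positive. Under the threshold in Section 2.8, every one of those tests would be called significant or not at the same level and with the same standing.

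The aim and the expected conclusion are both worded by domain, so a chance finding on one instrument could easily be written up as a domain-specific benefit of the programme. An ineffective programme has a well above 5% chance of producing at least one such result. The issue is the family of endpoints: it remains even if one model and one time point are fixed.

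**Working it through.** **Inputs from the article.** Per-test level 0.05 (Section 2.8; sidedness is not stated, two-sided is assumed here). Seven instruments (Table 2), of which six are domain measures once the ICOPE total is set aside. Sample size inputs from Section 2.2: f = 0.25, α = 0.05, power 0.90, three measures, correlation among repeated measures 0, 70 evaluable participants.

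**Assumption.** The article gives no correlation between instruments. A common correlation r from 0 to 0.8 is used as a range.

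**1. The plan's own figure.** The article states no familywise error rate; its one reproducible figure is the sample size. For the group × time interaction, λ = f² × N × m / (1 − ρ) = 0.0625 × 70 × 3 / 1 = 13.125, with df1 = (2 − 1)(3 − 1) = 2 and df2 = (70 − 2)(3 − 1) = 136. Power is 0.904 at N = 70 and 0.895 at N = 68, so the stated 70 reproduces. It allows for one test at 0.05 and names no outcome.

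**2. Chance of at least one p ≤ 0.05, no true effect, one test per instrument.** At r = 0 this is 1 − 0.95^k:

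- k = 7: 1 − 0.95⁷ = 0.302
- k = 6: 1 − 0.95⁶ = 0.265

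For r > 0 it is the probability that the largest of k equicorrelated |z| values exceeds 1.96:

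| Instruments | r = 0 | r = 0.2 | r = 0.5 | r = 0.8 |
|---|---|---|---|---|
| 7 (including ICOPE total) | 0.302 | 0.287 | 0.230 | 0.149 |
| 6 (domain instruments) | 0.265 | 0.254 | 0.207 | 0.139 |

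With the 2-df interaction test in place of a single contrast, the results are close: 0.302 to 0.154 for seven instruments and 0.265 to 0.142 for six, over r from 0 to 0.8.

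**3. False benefit only.** On a single contrast, half of each test's error points towards harm, so the nominal rate for a false claim of benefit is 0.025. For six domain instruments at r = 0: 1 − 0.975⁶ = 0.141. At r = 0.5 it is 0.104 and at r = 0.8 it is 0.069.

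**4. One declared primary.** If a single measure is primary and tested once, its error is 0.05 whatever the other six show. The figures for six instruments then describe the domain tests alone.

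**5. Cost of controlling the domain family.** The first Holm step for six tests is 0.05 / 6 = 0.0083. With the same λ = 13.125, df 2 and 136, power at 0.0083 is 0.73, against 0.90 at 0.05.

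**The case against.** The strongest reply is that the primary outcome is already clear. The abstract names one outcome and a mean difference, only the ICOPE total expresses intrinsic capacity as one number, and the Highlights describe an assessment based on that tool. On this natural reading the primary error is 5%, and only the domain tests are left uncontrolled. Much of this stands: the ICOPE total is the obvious candidate, and a reader who infers that the primary test itself runs at an inflated error goes further than the text allows. But no sentence makes the link, and Section 2.6.1 describes the intrinsic capacity assessment through six domains, so the other reading stays open.

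A reader might also infer that any one significant instrument counts as success. The Conclusion does not say so. It lists the areas together as something that may improve, and makes the benefit conditional on the programme proving effective. It is an expectation, not a decision rule.

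A single headline such as a 23% chance of a false domain claim is tempting too. That value needs seven instruments and an assumed correlation of 0.5, and it counts the ICOPE total as a domain. It also includes false positives in the direction of harm.

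Finally, detailed multiplicity handling is often left to a full protocol or analysis plan that is not shown, and its absence from an article is no fault. That is fair. The point rests instead on what the article does state: a primary outcome without a measure, and one significance rule for every test.

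**Conclusion.** The concern holds in limited form. The named primary outcome is not tied to the composite score that the article itself defines, the seven measures are unranked, and the stated threshold gives all of them equal standing.

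The resulting error, for either the seven instruments or the six domain instruments, is roughly three to six times the stated 0.05, and the rate of false benefit among the six domain instruments is about three to six times its nominal 0.025. These sizes assume one test per instrument, no true effect on any of them, and a common correlation between 0 and 0.8. Testing T1 and T2 separately, or using the overlapping tests in Section 2.8, could raise them. They do not show an inflated primary error if the ICOPE total is taken as primary.

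**What to change.** In Sections 2.6.1 and 2.8, state before unblinding that the ICOPE total score is the sole primary endpoint, tested at 0.05, and that it alone decides whether the programme worked.

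Label MMSE, SPPB, MNA, visual acuity, hearing and PHQ-9 as secondary, and choose one of two treatments for them:

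- report estimates with 95% confidence intervals and make no confirmatory claim; or
- if domain claims are wanted, test the six by Holm's procedure at a family level of 0.05, only after a significant primary result.

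Word the domain conclusions to match the choice.

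The change needs no extra data or participants. The primary test level and the sample size calculation stay as they are. The real cost falls on domain claims: under the second option, power at the first Holm step is about 73% instead of 90% on the article's own inputs, before allowing for the requirement that the primary be significant. The first option avoids that threshold but gives up confirmatory domain claims.
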